Participants will be excluded if they have anxiety states induced by physical conditions such as hypertension, Sjögren's syndrome, hyperthyroidism, or coronary heart disease. Additionally, individuals currently taking medications that may cause anxiety or those experiencing withdrawal symptoms from long-term use of anti-anxiety medications will be excluded. Anxiety states linked to other mental disorders will also be grounds for exclusion. Patients with severe liver or kidney dysfunction who cannot adhere to the medication regimen, as well as those known to be allergic to any components used in this study, will not be eligible. Furthermore, pregnant or breastfeeding women will be excluded from participation.

Inclusion Criteria for Healthy Participants

Participants must be between 18 and 65 years old, regardless of gender, and should be right-handed. They must be in good health, without any physical discomfort in the past month. Individuals who have undergone central nervous system stimulation, such as repetitive transcranial magnetic stimulation (rTMS), transcranial direct current stimulation (tDCS), or peripheral nervous system stimulation, such as acupuncture or electroacupuncture, will be excluded. Additionally, candidates must have no history of illegal drug use or alcohol abuse. All participants must voluntarily sign the informed consent form and agree to take part in the survey.

Randomization and Assessor-Blinding

Patients with GAD will be randomly assigned to either the treatment group or the control group using computer-generated random numbers. The random sequences, identified with unique labels, will be sealed in opaque envelopes, which will only be opened upon the enrollment of a participant. The sequence generation and allocation will be carried out by independent personnel who are not involved in the trial. Healthy participants will be enrolled as normal controls, without undergoing randomization.

Blinded assessments will be performed, with patients receiving treatment in distinct settings. Efficacy will be evaluated by a third party who is not privy to the group assignments. During data aggregation, blinded statistical analysis will be conducted. Throughout the study, researchers, clinical operators, efficacy evaluators, and data statisticians will maintain separation to ensure the integrity of the blinding process.

Sample Size

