Based on prior research, the Hamilton Anxiety Rating Scale (HAMA) score for the medication group was 18.61±3.17 [14]. The HAMA score for the treatment group is anticipated to decrease by 2.76 points. With a two-sided significance level (α) of 0.05 and a power of 90%, the required sample size was calculated using PASS 2021 software. This resulted in a needed sample size of N1=29 for the treatment group and N2=29 for the control group. Taking into account a potential dropout rate of 20%, a minimum of 35 subjects per group is needed, amounting to a total of at least 70 subjects. In addition, 35 healthy participants will be included in the study.

Intervention

Treatment Group GAD Patients

The medication regimen for this study will consist of oral escitalopram (Bailex) (Sichuan Kelun Pharmaceutical Co., Ltd., China; approval no.: National Drug Standard H20080788; specification: 10 mg × 10 tablets) [15]. Each participant will take 10 mg once daily at 09:00 AM for a duration of eight weeks.

In addition to the medication, participants in the treatment group will receive abdominal massages. The massage procedure will follow guidelines from the "Tui Na" textbook [16] edited by Fang Min and Wang Jingui (5th edition, "14th Five-Year Plan" for higher education in TCM). Participants will lie in a supine position while the practitioner performs rhythmic circular motions on the abdomen with the palm, 5 minutes clockwise and 5 minutes counterclockwise, at a frequency of 120 times/min. This is followed by finger massage on Zhongwan, Tianshu, Qihai, and Guanyuan points for 5 minutes at a frequency of 160 times/min. The total treatment time is approximately 15 minutes, conducted once daily, five days a week, for eight weeks.

To ensure the quality of the abdominal massage and the precise location of the acupoints, several measures will be implemented. Prior to the trial, [name] massage techniques, including force and frequency, will be calibrated using the YF-3 Hand Technique Measurement Instrument to create a standardized model. During the trial, experienced physicians with over 10 years of clinical practice will carry out the procedures. Additionally, all operators will receive training to ensure their techniques align with the model established by the YF-3 instrument.

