After GAD patients are enrolled, they will initially receive two weeks of abdominal massage treatment by a Tui Na doctor, followed by training in the technique. After two weeks, the force applied by patients during self-massage will be measured to standardize the technique. For the remaining six weeks, patients will visit the clinic once a week for treatment, with the remaining sessions performed at home. Patients will receive a video tutorial on abdominal massage and are required to upload videos and photos of their self-treatment for review. If inconsistencies are found, the doctor will provide online guidance. If the technique is corrected after three attempts, the patient will remain in the study; otherwise, they will be considered a dropout.

The acupoints utilized in this study are defined according to the 2021 national standard (GB/T12346-2021) titled "Names and Locations of Acupoints."[17] These acupoints include Zhongwan (CV12), which is situated in the upper abdomen, 4 cun above the navel along the anterior midline; Tianshu (ST25), located at the level of the navel, 2 cun lateral to the anterior midline; Qihai (RN6), found in the lower abdomen, 1.5 cun below the navel on the anterior midline; and Guanyuan (CV4), positioned 3 cun below the navel on the anterior midline. A map illustrating the locations of these acupoints is provided in Figure 3.

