**Figure 3 FIG3:**
[figure not shown]
Acupoint location diagram.

Control Group GAD Patients

Medication includes oral escitalopram (Bailex) (Sichuan Kelun Pharmaceutical Co., Ltd., China; approval no.: National Drug Standard H20080788; specification: 10 mg × 10 tablets), 10 mg once daily at 09:00 AM for eight weeks.

Healthy Participants

Healthy participants will not receive any treatment. They will be screened based on their medical history and HAMA scores. General information and HAMA scores will be recorded. Upon enrollment, EEG and stool samples will be collected from healthy participants.

Statistical analysis

This study will conduct statistical analysis based on the principle of intention-to-treat (ITT), including all patients who entered randomization and were not excluded in the statistical analysis. The efficacy endpoints will be analyzed using the full analysis set (FAS), supplemented by the per-protocol set (PP). Safety endpoints will be analyzed using the safety set (SS).

IBM SPSS Statistics for Windows, Version 26 (Released 2019; IBM Corp., Armonk, New York, United States) will be used for statistical processing. Measurement data will first be tested for normal distribution and homogeneity of variance. Data that meet the normal distribution and homogeneity of variance will be statistically described using the mean ± standard deviation (x̄±s), and data that do not meet the normal distribution and homogeneity of variance will be statistically described using the median (M) and the 25th and 75th percentiles (P_25_, P_75_).

For the comparison of measurement data between two groups, a paired two-sample t-test will be used for data that meet the normal distribution, and a rank-sum test will be used for data that do not meet the normal distribution. For the comparison of data at different time points after treatment with pre-treatment data, a paired t-test will be used for data that meet the normal distribution, and a rank-sum test will be used for data that do not meet the normal distribution. For the comparison of measurement data among multiple groups, a one-way ANOVA will be used for data that meet the normal distribution, and a rank-sum test will be used for data that do not meet the normal distribution.

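### Massage-arm patients whose self-massage technique stays uncorrected become dropouts: a post-randomisation removal possible in one arm only, at odds with the stated intention-to-treat principle

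*Protocol article*

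**What the plan says.** - **Allocation.** Under Randomization and Assessor-Blinding, the random sequences are "sealed in opaque envelopes, which will only be opened upon the enrollment of a participant". Allocation is therefore fixed at enrolment.
- **Massage arm.** Under Treatment Group GAD Patients, massage is added to escitalopram: "In addition to the medication, participants in the treatment group will receive abdominal massages". A practitioner gives it for two weeks and the patient is trained. Then: "For the remaining six weeks, patients will visit the clinic once a week for treatment, with the remaining sessions performed at home". Patients upload recordings of their home sessions and a doctor gives online guidance if the technique is off.
- **Technique rule.** "If the technique is corrected after three attempts, the patient will remain in the study; otherwise, they will be considered a dropout".
- **Control arm.** Under Control Group GAD Patients, treatment is escitalopram alone, "10 mg once daily at 09:00 AM for eight weeks". The article states no matching performance check or removal rule for this arm.
- **Analysis sets.** Statistical analysis invokes intention-to-treat and describes the population as "including all patients who entered randomization and were not excluded in the statistical analysis". Efficacy is analysed in the FAS, with the per-protocol set as a supplement.
- **Sample size.** The article gives "the Hamilton Anxiety Rating Scale (HAMA) score for the medication group was 18.61±3.17", an anticipated difference of 2.76 points, 29 per arm, and 35 per arm after a 20% dropout allowance.

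**The concern.** The rule makes staying in the study the opposite of being a dropout. A patient who is willing and able to be assessed is thus counted out for performing the allocated treatment poorly. Skill and effort at self-massage may go with motivation, symptom severity or tablet-taking, all of which may relate to the HAMA score. If these patients have no end-of-treatment assessment or are left out of the analysis, the massage arm becomes a selected group, and this rule makes no corresponding selection among controls. Concealed allocation and blinded assessment do not help, because the selection comes after allocation.

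The intention-to-treat wording gives no protection. Covering randomised patients who have not been excluded is circular unless the permitted exclusions are named.

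At stake is the between-arm HAMA comparison in a trial of 70 patients. A later analysis plan can decide how missing values are treated, but it cannot recover a week-8 HAMA that was never taken.

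**Working it through.** **1. Does the rule act after randomisation, and in which arm?** Envelopes are opened at enrolment. Self-massage at home fills weeks 3 to 8. Only the massage arm performs it. So the rule is post-randomisation and confined to one arm.

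**2. Does the text keep these patients in the analysis?** The rule contrasts remaining in the study with being a dropout. The sample-size section recruits extra patients to offset dropouts, so it plans for them not to count towards the 29. No section says that technique failures are still assessed or kept in the FAS, and no section says that they are removed from it.

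**3. The plan's own figure.** Inputs from Sample Size: difference 2.76, SD 3.17, two-sided α 0.05, power 90%. A two-sample t-test (noncentral t) gives power 0.892 with 28 per arm and 0.903 with 29, so 29 reproduces. The stated 35 reproduces as 29 × 1.2 = 34.8, rounded up.

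**4. Is the harm lost power?** Hardly. At the planned effect, power is 0.948 with 35 v 35 and 0.922 with 28 v 35, that is, after losing 7 massage patients. The issue is bias.

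**5. Size of the bias.** Two inputs are not in the documents and are assumed: the fraction f of the massage arm removed, and the gap g in final HAMA between those removed and those kept. With no true effect and the same kinds of patient in both arms:

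spurious benefit = f × g

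- Smallest case: 0.05 × 1 = 0.05 points.
- Largest case: 0.20 × 3 = 0.6 points, and 0.6 / 2.76 = 22% of the planned effect.
- g = 0: no bias, and error stays at 5%.

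**6. Effect on the two-sided 5% error.** Simulation of 40,000 trials per setting, 35 per arm, SD 3.17, no true effect, a poorer-scoring subgroup present in both arms but removed from the massage arm only, two-sample t-test:

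| Gap g (HAMA points) | 10% removed: bias, error | 20% removed: bias, error |
|---|---|---|
| 1 | 0.1, 5.2% | 0.2, 5.8% |
| 2 | 0.2, 5.7% | 0.4, 7.6% |
| 3 | 0.3, 6.5% | 0.6, 10.5% |

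With 5% removed, the bias is at most 0.05 × 3 = 0.15 points and the error at most about 5.4%.

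**7. Cross-check of the largest case without simulation.** With 7 of 35 removed and g = 3, the standard error is 3.17 × √(1/28 + 1/35) = 0.804. The noncentrality is 0.6 / 0.804 = 0.75 on 61 degrees of freedom, which gives a rejection rate of 11.4%. This is close to the simulated 10.5%; the small difference is simulation noise and the SD being held at 3.17 in both arms. Both support an upper end of about 11%.

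**The case against.** The strongest reply is that the article calls these patients dropouts and nothing more. It does not discard their data, withhold their week-8 assessment or take them out of the FAS. It states intention-to-treat and makes the FAS the main efficacy set. How dropouts are handled there is something a condensed article may leave to a full protocol or analysis plan. **This stands in part.** A reader might infer that technique failures are certainly deleted and that the intention-to-treat analysis is already broken; the text does not go that far. What remains is a rule that ends study participation without saying that outcomes are still collected, which no analysis plan can repair afterwards.

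The exclusion phrase in the intention-to-treat definition is not tied to technique failure and could refer to, say, patients found ineligible. **That stands too.** The fault is that the phrase names no grounds, so it also admits this one.

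A reader might infer that the control arm has no adherence filter at all. The article gives none, but general withdrawal criteria may have been condensed. What the text supports is that this particular rule cannot apply to controls.

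A reader might also infer that the bias must favour massage. Nothing in the documents shows that technique failures do worse. Patients who improve early might practise less carefully, and losing them would count against massage.

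Finally, a 3-point gap is large: 3 / 3.17 = 0.95 SD, more than the planned effect. Removing 20% (7 of 35) would use the whole dropout allowance on technique failure alone. Training, force measurement, weekly visits and three correction attempts should keep failures fewer. **This stands**, and is why the size is given as a range that starts near zero.

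**Conclusion.** The concern holds in a limited form. The protocol fixes a post-randomisation removal that depends on performance of the assigned treatment and can occur only in the massage arm. It does not provide for continued assessment of those removed, and its intention-to-treat definition leaves room to omit them. That conflicts with the stated principle and can bias the HAMA comparison.

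Under assumed gaps of 1 to 3 points and 5 to 20% of the massage arm removed, the spurious benefit is about 0.05 to 0.6 points and the two-sided error about 5 to 11%, so the effect runs from negligible to moderate. These figures also assume that the removed patients contribute no final HAMA to the analysis and that they score worse than those kept. If they score better, the bias reverses; if they score the same, there is none. Neither the failure rate nor the gap can be read from the documents.

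The repair belongs in the protocol, before patients are followed, because it concerns which outcomes are collected.

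**What to change.** - **Technique rule.** Replace the dropout consequence: a patient whose technique remains uncorrected is recorded as non-adherent (a protocol deviation), stays in follow-up, and has the week-8 HAMA, EEG and other planned assessments. This concerns follow-up and analysis only and says nothing about how treatment should be managed.
- **Analysis sets.** Define the intention-to-treat population and FAS as all randomised patients, analysed in their assigned arm, and delete the closing condition about patients not having been excluded. Exclude technique failures from the per-protocol set only; that set already addresses massage performed as intended.
- **Terminology.** Keep the term dropout for withdrawn consent or loss to follow-up.

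**Cost.** A few sentences of amendment and end-of-treatment assessments for a few patients who would otherwise have left. The estimated effect may be somewhat smaller, because it will include patients who did not master the technique. The recruitment target need not change.

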**Figure 3 FIG3:**
[figure not shown]
Acupoint location diagram.

Control Group GAD Patients

Medication includes oral escitalopram (Bailex) (Sichuan Kelun Pharmaceutical Co., Ltd., China; approval no.: National Drug Standard H20080788; specification: 10 mg × 10 tablets), 10 mg once daily at 09:00 AM for eight weeks.

Healthy Participants

Healthy participants will not receive any treatment. They will be screened based on their medical history and HAMA scores. General information and HAMA scores will be recorded. Upon enrollment, EEG and stool samples will be collected from healthy participants.

Statistical analysis

This study will conduct statistical analysis based on the principle of intention-to-treat (ITT), including all patients who entered randomization and were not excluded in the statistical analysis. The efficacy endpoints will be analyzed using the full analysis set (FAS), supplemented by the per-protocol set (PP). Safety endpoints will be analyzed using the safety set (SS).

IBM SPSS Statistics for Windows, Version 26 (Released 2019; IBM Corp., Armonk, New York, United States) will be used for statistical processing. Measurement data will first be tested for normal distribution and homogeneity of variance. Data that meet the normal distribution and homogeneity of variance will be statistically described using the mean ± standard deviation (x̄±s), and data that do not meet the normal distribution and homogeneity of variance will be statistically described using the median (M) and the 25th and 75th percentiles (P_25_, P_75_).

For the comparison of measurement data between two groups, a paired two-sample t-test will be used for data that meet the normal distribution, and a rank-sum test will be used for data that do not meet the normal distribution. For the comparison of data at different time points after treatment with pre-treatment data, a paired t-test will be used for data that meet the normal distribution, and a rank-sum test will be used for data that do not meet the normal distribution. For the comparison of measurement data among multiple groups, a one-way ANOVA will be used for data that meet the normal distribution, and a rank-sum test will be used for data that do not meet the normal distribution.

For the comprehensive comparison of measurement data at different time points between two groups, a repeated measures ANOVA will be used if the data meet the sphericity assumption and a Friedman test will be used if the data do not meet the normal distribution. Count data will be statistically described using case number and composition ratio, and the comparison between groups will be performed using the χ² test. Rank data will be analyzed using the two-sample non-parametric rank-sum test. The significance level for all tests will be α=0.05.

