**Figure 2 FIG2:**
[figure not shown]
Schedule of enrollment, intervention, and assessments of this protocol. In the cells, "X" indicates that the examination was conducted at this time point; an empty cell signifies that the examination was not conducted at this time point. Cells connected by two triangles represent that treatment was administered during this period. HAMA: Hamilton Anxiety Scale; HAMD: Hamilton Depression Scale; SCL-90: Symptom Checklist 90; EEG: electroencephalogram

This randomized clinical trial is aligned with the principles of the Declaration of Helsinki. It has received approval from the Ethics Committee of the First Teaching Hospital of Tianjin University of Traditional Chinese Medicine (TYLL2024[Z]041) and has been registered on the International Traditional Medicine Clinical Trials Registry Platform (ITMCTR2024000140). All participants in this study will be voluntary participants and will sign informed consent forms prior to the commencement of the trial.

Participants

Diagnostic Criteria

The diagnostic criteria for Western medicine in this study are based on the International Classification of Diseases-11 (ICD-11) [11] and the Diagnostic and Statistical Manual of Mental Disorders-5 (DSM-5) [12]. The TCM diagnostic criteria draw on the 2008 Guidelines for the Diagnosis and Treatment of Common Diseases in Internal Medicine (TCM disease diagnosis section) [13] for depression (Appendix A).

Inclusion Criteria for GAD Patients

Participants must meet the previously mentioned Western and Traditional Chinese Medicine diagnostic criteria for GAD. They should be aged between 18 and 65 years, regardless of gender, with a HAMA score ranging from 14 to 29 prior to the trial, indicating mild to moderate GAD. Additionally, they must not have taken any other anti-anxiety or psychiatric medications in the past month and must voluntarily sign an informed consent form.

Exclusion Criteria for GAD Patients

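### Normality and variance pretests on the trial's own data decide how HAMA is summarised, and normality decides whether means or ranks are tested, so the effect measure of an outcome sized on a mean difference is not fixed in advance

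*Protocol article*

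**What the plan says.** In the protocol article (Materials and methods, Statistical analysis), "Measurement data will first be tested for normal distribution and homogeneity of variance". Data that pass are described by mean and standard deviation. For the rest, "data that do not meet the normal distribution and homogeneity of variance will be statistically described using the median (M"), together with the quartiles.

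The choice of test follows in the next paragraph and depends on normality alone: a t-test if the data are normal, a rank-sum test if not. The same switch governs the comparison with pre-treatment values. For the comparison of two groups across time points, the alternatives are repeated measures ANOVA and, if the data are not normal, a Friedman test. None of these rules makes an exception for HAMA, which the Primary outcome section names as a primary outcome.

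The Sample Size section is written in means: "the Hamilton Anxiety Rating Scale (HAMA) score for the medication group was 18.61±3.17" and "The HAMA score for the treatment group is anticipated to decrease by 2.76 points". The result is "N1=29 for the treatment group and N2=29 for the control group", raised to 35 per arm for dropout.

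The inclusion criteria admit patients "with a HAMA score ranging from 14 to 29 prior to the trial".

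**The concern.** A trial sized on a difference in means should commit to estimating that difference. Here a significance test on the outcome data comes first. If HAMA fails it, the stated route leads to medians, quartiles and a rank-sum test. A rank-sum test asks whether scores in one arm tend to be lower than in the other. It does not estimate a difference in points, and it coincides with a test of means only under extra assumptions such as a pure shift. The reader could then be left without the quantity behind the 2.76-point assumption, and that choice would have depended on the data.

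The two rules also use different conditions, so the summary and the test can disagree for the same variable.

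**Working it through.** **1. What the trial was sized for.** Inputs from the Sample Size section: difference 2.76, SD 3.17, two-sided 0.05, power 90%.

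Normal approximation: n = 2 × (1.960 + 1.2816)² × (3.17 / 2.76)² = 2 × 10.507 × 1.319 = 27.7, so 28 per arm. The exact two-sample t-test (noncentral t) has power 89.2% at 28 and 90.3% at 29 per arm. The stated 29 is therefore reproduced as an independent two-sample comparison of means.

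**2. How often the switch would occur.** Assumptions: Shapiro-Wilk at 0.05 in each arm (no test is named), integer-rounded scores, SD 3.17 in both arms, rank-sum test if either arm fails. The skewed shapes are illustrative. Shares of simulated trials in which at least one arm fails (6,000 trials per setting, no true difference):

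| Week-8 HAMA | 29 per arm | 35 per arm |
|---|---|---|
| Normal, rounded | 17% | 19% |
| Skewness 0.5 | 37% | 42% |
| Skewness 1.0 | 76% | 85% |

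The first row can be checked by hand. Two 5% tests alone give 1 − 0.95² = 9.75%. Rounding raises the single-arm rejection rate to 9.3% at 29 and 9.6% at 35, and 1 − 0.907² = 17.7%, 1 − 0.904² = 18.3%.

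**3. Effect on error rates.** At 29 per arm with a true difference of 0 or 2.76:

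| Shape | Fixed t-test: size, power | Pretest then t or rank-sum: size, power |
|---|---|---|
| Normal | 4.9%, 90.1% | 4.9%, 89.9% |
| Skewness 0.5 | 5.2%, 90.1% | 5.5%, 90.3% |
| Skewness 1.0 | 4.4%, 89.4% | 4.9%, 92.2% |

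Across all settings, including 35 per arm, the size of the two-stage procedure was 4.8% to 5.7%. The pretest neither protects the error rate nor damages it materially.

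**4. Where the entry window matters.** The 14 to 29 limit applies before treatment. Post-treatment HAMA can take any value from 0 to 56 (Primary outcome section). The window therefore cuts the baseline scores only. It can push analyses that include baseline (pre-post test, comparison across time points) to the non-parametric branch, but not a comparison of week-8 scores alone. How often depends on the assumed baseline shape. If 18.61 and 3.17 describe the distribution before the cut, one arm of 35 fails in 19.8% of cases, so at least one of two fails in 1 − 0.802² = 36%. Across other assumed shapes the single-arm rate ran from 8% to 84%.

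**5. The two rules side by side.**

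| Data | Described by | Tested on |
|---|---|---|
| Normal, equal variance | mean, SD | means |
| Normal, unequal variance | median, quartiles (if failing either condition counts) | means |
| Not normal | median, quartiles | ranks |

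In the second row the summary and the test do not match.

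**The case against.** The strongest reply is that the pretest does no measurable statistical harm. This stands: size and power are essentially unchanged, and nothing in the text forbids adding a mean difference. It is also true that an article may leave detail to a fuller plan, so the absence of a named unequal-variance test or confidence interval is not itself a fault. But the article does not leave the choice open. It states a rule, applies it to all measurement data, and that rule makes the HAMA analysis depend on the data.

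The row with unequal variances can be called a wording ambiguity. That is fair: it affects description only.

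A reader might infer more than the documents support:

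- *That the entry window makes HAMA non-normal, so the mean difference will not be reported.* The window does not cut week-8 scores, so this does not follow. A baseline failure rate as high as 74% at 35 per arm can be obtained, but only by reading 18.61 ± 3.17 as the baseline distribution after the cut. The protocol gives no time point for that figure.
- *That the variance pretest chooses the test.* As written, it governs only the description.
- *That unequal variances distort the primary comparison.* Marked distortion (size 1.6% or 10.9%) appears with 70 against 35 subjects and an assumed 2:1 SD ratio. That is patients against healthy controls, not the equal-sized randomised arms, and the documents give no such ratio.

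**Conclusion.** The concern holds in a limited form. The stated rules let tests on the trial's own data choose the summary of HAMA, and let normality choose between means and ranks, while the sample size is reproduced as a comparison of means. Under the assumptions of step 2 of the working, the switch would occur in about 17 to 19% of trials even with normal week-8 scores, and more often with skewed ones. The size depends on the assumed test and shapes; that the effect measure is not fixed follows from the text alone. The harm lies in what is estimated and reported, not in type I error (about 5%) or power (about 90%). The change is worth making because it is cheap, not because the planned test would be invalid.

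**What to change.** State in advance, regardless of any pretest:

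- The HAMA comparison is the between-arm difference in mean week-8 score with a 95% CI, from an independent-samples analysis with an unequal-variance (Welch) standard error. The section currently names a paired t-test for two groups, so that sentence needs rewording in any case.
- HAMA is always reported as mean and SD in each arm; quartiles may be added.
- Normality and variance tests are removed as gates for HAMA.
- The rank-based result is given as a sensitivity analysis only.

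Cost: analysis wording only. The required number stays at 29 per arm. With equal arms the Welch and pooled t statistics are identical and differ only slightly in degrees of freedom. One downside: for markedly skewed EEG or microbiota variables, a rank-based or transformed analysis has to be named in advance, variable by variable.
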